### Immune cell phenotyping

To characterize immune profiles beyond cytokine clusters, we intend to perform both flow cytometry and fluorescence-activated cell sorting (FACS) using the acquired PBMCs. Based on changes reported in prior ECT studies [84, 147–152], we will use surface and intracellular markers to characterize immune cell subpopulations.

### Metabolic and endocrine profiling

In addition to humoral and cellular immune profiling, we aim to characterize metabolic and endocrine states using established clinical and blood markers (e.g., BMI, BP, serum lipids, leptin and ghrelin, PBMC membrane proteins like CD220 or GLUT1, corticotropin-releasing hormone, and cortisol). This approach aligns with the growing evidence linking immunometabolic and neuroendocrine dysregulation to MDD [153–158].

## Study hypotheses and objectives

The primary hypothesis of the DetECT study is that there exists a joint biological function and clinically meaningful connection between changes in gene expression and regulation, immunometabolic conditions, purinergic signaling, and CNS-derived exosome release in TRD patients receiving ECT. The secondary hypothesis is that these changes can be utilized to predict and monitor ECT outcome in TRD patients.

The main study objective is therefore to identify biological, psychological, socioeconomic, and clinical parameters (biomarkers) that provide detailed information about the general or individual factors of ECT success and the biobehavioral disease subgroups these changes are linked to. The DetECT data may also serve as a cornerstone for the development of a biologically founded, multimodal prognosis model for ECT use in TRD. As a subordinate objective, we hope to generate novel insight into the molecular effects of ECT in TRD using the generated omics data. Taken together, we believe that the DetECT results can aid precision medicine approaches for ECT application and to boost its social as well as clinical acceptance.

## Power calculation

In complex psychiatric illnesses, such as MDD, which arise from the reciprocal interaction of endogenous and exogenous influences (interaction: genes x environment) [159], the effect of single parameters is small. Only the interaction of many and qualitatively heterogeneous components leads to the disease. The best-known explanatory model is the diathesis-stress model, in which the interaction of individual vulnerability (biological and psychosocial) and external influences is acknowledged. Therefore, and due to the exploratory and multiomics approach of the DetECT study focusing on unstudied parameters, sample size calculation cannot simply be performed based on preexisting study results. Accordingly, we have based our power calculation on the clinical ECT efficacy [55, 56], as it is a composite indicator of the interplay of multiple ECT-induced biological mechanisms and their effect sizes, respectively. Using G*Power 3 Software comparing responders with non-responders assuming a moderate effect size of *d* = 0.5, a significance level *α* = 0.05, and a power of 1–*β* = 0.8, we computed a sample size of *n* = 134 [160].

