Beyond conventional pharmaco- and psychotherapy, neurostimulation techniques such as electroconvulsive therapy (ECT) are widely available, safe, and powerful treatment options in psychiatry [30–33]. About 80% of all ECTs are performed in patients with MDD [34, 35]. Though ECT should always be preceded by an individual risk–benefit assessment [36], studies and meta-analyses overall report markedly favorable response rates as high as 79% and remission in up to 70% of cases [37–39]. In severe and psychotic depressive episodes, Petrides et al. have even reported remission in 95% of their participants [40]. ECT is also a highly effective treatment option for TRD [37], with an efficacy comparable to the general response rates seen in treatment-responsive depression [41]. Studies and meta-analyses indicate an ECT-related response in 56–85% and a remission in about 48% of patients with prior medication failure or TRD, respectively [27, 41–44]. This response rate in TRD is similar to the response rates reported for antidepressant drugs and psychotherapy overall in non TRD patients of about 50–60% [45–51]. It is thus not surprising that the mean effect size of ECT (d ≈ 0.9–1.3) is higher than the one of antidepressants (*d* ≈ 0.37) or psychotherapy (*d* ≈ 0.75) [52–58]. ECT-induced remission is commonly achieved early during treatment (~ 3 weeks after ECT start) [27, 59]. ECT is also known to significantly reduce the risk of suicide [33, 60–62]. Due to the high recurrence rates of up to 81% after acute-phase ECT, maintenance sessions are recommended and performed in gradually decreasing frequency to preserve the initial therapy success [36, 39, 63–68]. During an ECT series, sub-/acute side effects, such as headaches, muscle soreness, nausea, transient hypertension, anterograde and retrograde amnesia (especially ± 3 days around the ECT), and postictal confusion, rarely a delirium, can occur due to the applied current and induced seizure apart from general anesthesia risks [69, 70]. These adverse effects are reversible and short-lived in the majority of cases (< 1 h post-ECT) [69]. The frequency of cognitive or memory side effects is associated with patient and disease characteristics as well as the ECT stimulation paradigm and intensity (e.g., strong, bitemporal stimulation over a long period of time: increased memory disturbance) [70–73]. On average, however, cognitive performance tends to remain the same or improve after ECT treatment [71, 74, 75]. Both magnetic resonance imaging and autopsy studies as well as animal experiments have not demonstrated any organic brain damage due to ECT [76–80]. The balance between strong clinical effects and a tolerable side effect profile makes ECT the gold standard of stimulation methods, provided appropriate patient selection [55, 75, 81, 82].

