## Prospective statistical analysis

The statistical analysis of the DetECT study mainly focuses on comparing ECT responders with non-responders (internal control group) within the sample. Clinical response indicated by overall and sub-domain changes in psychometry will serve as main dependent variables and analyses focus on within-subject changes over time. On the one hand, we aim to use variance and correlation analyses (e.g., repeated-measures ANOVA, Pearson’s r and correlation matrices), regression models (e.g., linear or logistic regression), and principal component analysis to first identify both significant main and interaction effects between biobehavioral parameters and treatment response. These analyses will be performed for all measures pre-, during, and post-treatment. Aside from using single parameters and the area under the curve as independent variables, we will employ index and score approaches (e.g., inflammatory indexing and Z scores) to allow combined analyses of functionally connected processes. Following these steps, we plan to employ linear mixed models (LMM) to examine if a single or parameter cluster is linked to remission, treatment response, failure, and side effects. As described above, we will also use single and combined as well as over time parameters, indices, or scores to perform LMM. Factors like the SES, comorbidities, smoking, concomitant pharmacological treatment (both general and psychiatry specific), and mode of ECT application (e.g., right-unilateral vs. left-anterior-right-temporal) will be used as covariates. Multiple comparisons correction will be applied. To further ensure that the identified associations are not only statistically significant, but also represent a relevant underlying biological mechanism, we will report both significance (p value) as well as effect size (e.g., Cohen’s d or comparable measures) in prospective DetECT publications, as recommended for instance by Goodman et al. 2019 [161].

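### The stated 80% power covers one uncorrected responder comparison at an assumed d = 0.5 and does not carry over to the multiplicity-corrected marker tests that the plan describes

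*Protocol article*

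**What the plan says.** The Power calculation section of the protocol article first explains why earlier results cannot simply be used: in illnesses with many interacting causes, "the effect of single parameters is small", and the study looks at parameters not studied before. It then gives its substitute: "Accordingly, we have based our power calculation on the clinical ECT efficacy [55, 56"], on the ground that efficacy reflects many ECT-induced mechanisms together. The calculation itself is described as "comparing responders with non-responders assuming a moderate effect size of" d = 0.5, with "a significance level *α* = 0.05" and power 0.8, giving n = 134. The test, its sidedness and the responder share are not named.

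The Prospective statistical analysis section plans ANOVA, correlation, regression, principal components and linear mixed models. They cover all measures before, during and after treatment, using single parameters, areas under the curve, indices and clusters, against remission, response, failure and side effects. It states: "Multiple comparisons correction will be applied". The method and the number of tests are not given. The sample analytics sections list genotyping, epigenetics, RNA sequencing, exosomal miRNA, cytokines, purines, immune cells and metabolic and endocrine markers.

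The Introduction reports that "the mean effect size of ECT (d ≈ 0.9–1.3) is higher than the one of antidepressants", and gives response rates of 56–85% after medication failure or in TRD.

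**The concern.** Two statements in the same article do not fit together. The sample size rests on one comparison at alpha 0.05, yet the comparisons to be made are many and will face a smaller alpha. The 80% figure is the only quantitative support for 134 patients, so a reader will naturally attach it to the marker tests.

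The effect size has a separate weakness. Efficacy measures how much symptoms improve with ECT. The powered quantity is how far responders and non-responders differ, and under this plan that difference is in a biological or clinical marker. The first does not determine the second.

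At stake is how the results are read. With power well below 80%, a marker that shows no signal is weak evidence of no association, and markers that pass the corrected threshold will tend to have overestimated effects. The Study timeline section looks towards clinical implementation of the identified biomarkers, so the selected markers are the ones that would be carried forward.

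**Working it through.** **Inputs.** From Power calculation: d = 0.5, alpha = 0.05, power 0.80, N = 134. From the Introduction: response 56–85%. Assumed: two-sided tests; Bonferroni with m = 2, 4, 20 or 100 tests; splits of 67/67 (1:1), 80/54 (60% responders), 94/40 (70%) and 114/20 (85%). A 56% share gives 75/59.

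**Step 1: reproduce 134.**
- Normal approximation, 1:1: n per group = 2(1.960 + 0.842)²/0.5² = 62.8, so 63 per group and 126 in total.
- Exact t test, 1:1: 64 per group, 128 in total.
- Wilcoxon–Mann–Whitney, 1:1, efficiency 3/π: 67 per group, **134** in total (power 0.801).
- t test with a 60:40 split: 133 in total.
- One-sided: 100 (normal) or 102 (t).

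So 134 is reproducible, and the variants that give it or come within one patient of it are single two-sided tests at the full alpha of 0.05.

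**Step 2: power after correction.** The noncentrality is λ = d·√(n₁n₂/N), with 132 degrees of freedom, and the critical value c is the 1 − 0.05/(2m) quantile of t. Power = P(noncentral t > c).
- 67/67: λ = 0.5·√(4489/134) = 2.894
- 80/54: λ = 0.5·√(4320/134) = 2.839
- c = 1.978 (m = 1), 2.267 (m = 2), 2.532 (m = 4), 3.082 (m = 20), 3.569 (m = 100)

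| Tests m | Power, 67/67 | Power, 80/54 |
|---|---|---|
| 1 | 0.82 | 0.80 |
| 2 | 0.73 | 0.72 |
| 4 | 0.64 | 0.62 |
| 20 | 0.43 | 0.41 |
| 100 | 0.26 | 0.24 |

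**Step 3: effect of the responder share, one uncorrected test, d = 0.5.**
- 56% (75/59): λ = 2.873, power 0.81
- 70% (94/40): λ = 2.649, power 0.75
- 85% (114/20): λ = 2.063, power 0.53

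**Step 4: effect detectable with 80% power at N = 134**, solving the Step 2 formula for d.

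| Tests m | 67/67 | 80/54 | 94/40 | 114/20 |
|---|---|---|---|---|
| 1 | 0.49 | 0.50 | 0.53 | 0.68 |
| 4 | 0.58 | 0.60 | 0.64 | 0.82 |
| 20 | 0.68 | 0.69 | 0.74 | 0.95 |
| 100 | 0.76 | 0.78 | 0.84 | 1.07 |

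**Step 5: the basis for 0.5.** The Introduction's d ≈ 0.9–1.3 describes the benefit of ECT. The powered contrast lies within ECT-treated patients, between those who improve and those who do not. The article offers no step from one to the other, so 0.5 stands as an assumption only.

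**The case against.** The best defence is that the study is observational and labelled exploratory, that the article nowhere claims 80% power for corrected omics tests, and that it commits to reporting effect sizes beside p values. All of that is true and lowers the seriousness. It does not make the 80% figure apply to the tests planned, and reporting effect sizes does not remove the inflation that comes from selecting significant markers.

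Several stronger readings are tempting and are not supported:

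- **That no planned marker test can have 80% power.** This would follow only for true effects of 0.5 or less under a Bonferroni-type correction. The correction method is not named, and indices, areas under the curve, clusters and repeated measures might give larger effects or less noise. A true d of about 0.60 restores 80% at four tests. The article quantifies no such gain, but it does not exclude one.
- **That calling effects small and then assuming a moderate d is a contradiction.** The remark about small effects concerns how the illness arises, and the section uses it as its reason for taking a composite basis. Small is not quantified there.
- **That the efficacy range should have produced a d other than 0.5.** The article says it assumes 0.5. The 0.9–1.3 range sits under a shared block of citations, and what the two sources cited for the power calculation report cannot be seen.
- **That 134 is miscalculated.** It reproduces.
- **That a missing primary test or correction method is a fault.** A condensed article may leave both to the analysis plan.

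**Conclusion.** The concern holds in a limited form. The 80% applies to one uncorrected two-group comparison at an assumed d = 0.5 and a responder share near 50–60%. At that same d, one correction for two tests already brings power to 0.72–0.73, and for 20 tests it is 0.41–0.43. Across the 56–85% response range, a single uncorrected test has power between 0.81 and about 0.53. Clinical ECT efficacy is not evidence for a marker difference of 0.5.

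These figures rest on a two-sided t test, Bonferroni correction, assumed test counts, assumed splits and all 134 patients being analysable. A less strict correction or larger true effects would soften the loss. The problem is a mismatch between the power basis and the planned analyses. For an exploratory study it should be corrected, but it does not invalidate the design.

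**What to change.** In the Power calculation section:
1. State that 80% refers to one prespecified, uncorrected comparison of responders with non-responders at an assumed d = 0.5, and give the responder share assumed.
2. Withdraw clinical ECT efficacy as support for d = 0.5 and present the value as an assumption.
3. Report the detectable effect at the corrected alpha. With Bonferroni and splits of 67/67 to 80/54, it is d about 0.58–0.60 for 4 tests, 0.68–0.69 for 20 and 0.76–0.78 for 100. It is larger if 70–85% respond.
4. Describe corrected single-marker tests as exploratory, without 80% power.

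How to structure the test families, and whether to use composites, can be left to the analysis plan. The change needs wording only and no new data. Its downside is that the stated power becomes less favourable.

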## Abstract

Electroconvulsive therapy (ECT) is commonly used to treat treatment-resistant depression (TRD). However, our knowledge of the ECT-induced molecular mechanisms causing clinical improvement is limited. To address this issue, we developed the single-center, prospective observational DetECT study (“Multimodal Biomarkers of ECT in TRD”; registered 18/07/2022, www.clinicalTrials.gov, NCT05463562). Its objective is to identify molecular, psychological, socioeconomic, and clinical biomarkers of ECT response in TRD. We aim to recruit *n* = 134 patients in 3 years. Over the course of 12 biweekly ECT sessions (± 7 weeks), participant blood is collected before and 1 h after the first and seventh ECT and within 1 week after the twelfth session. In pilot subjects (first *n* = 10), additional blood draws are performed 3 and 6 h after the first ECT session to determine the optimal post-ECT blood draw interval. In blood samples, multiomic analyses are performed focusing on genotyping, epigenetics, RNA sequencing, neuron-derived exosomes, purines, and immunometabolics. To determine clinical response and side effects, participants are asked weekly to complete four standardized self-rating questionnaires on depressive and somatic symptoms. Additionally, clinician ratings are obtained three times (weeks 1, 4, and 7) within structured clinical interviews. Medical and sociodemographic data are extracted from patient records. The multimodal data collected are used to perform the conventional statistics as well as mixed linear modeling to identify clusters that link biobehavioural measures to ECT response. The DetECT study can provide important insight into the complex mechanisms of ECT in TRD and a step toward biologically informed and data-driven-based ECT biomarkers.

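### The stated 80% power at n = 134 holds only near the low end of the response rates the protocol cites; it falls from about 80% at 56% response to about 53% at 85%.

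*Protocol article*

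**What the plan says.** The Power calculation section bases the sample size on one two-group comparison. The sentence that gives it opens "Using G*Power 3 Software comparing responders with non-responders assuming a moderate effect size of". Its inputs are d = 0.5, a 5% level of significance and 80% power, and its result is a total of 134. The Abstract sets recruitment at the same number: "We aim to recruit *n* = 134 patients in 3 years". The Study timeline splits it into 10 pilot and 124 main-phase participants.

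The Prospective statistical analysis section makes this contrast the main focus, "comparing ECT responders with non-responders (internal control group) within the sample".

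The Introduction gives the response rate that the literature reports for patients with treatment resistance or earlier drug failure: "Studies and meta-analyses indicate an ECT-related response in 56–85" per cent. The power section attaches no response rate or group ratio to its result.

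**The concern.** In a randomised trial the allocation ratio is chosen. Here it is an outcome, because patients become responders or non-responders. For a fixed total, the precision of a two-group comparison is limited by the smaller group. At every rate in the cited range the smaller group is the non-responders, who would number 59 of 134 at 56% response and only 20 of 134 at 85%.

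A single unconditional figure of 80% therefore describes the comparison only for splits that are fairly even. If response is higher, a biomarker difference of d = 0.5 could be missed considerably more often than the stated one time in five. A reader who relies on the published power might then take a null result as stronger evidence of no association than it is.

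**Working it through.** **Inputs.** d = 0.5, α = 0.05, power 0.80 and N = 134 come from the Power calculation section. Response of 56–85% comes from the Introduction. The test and its sidedness are not stated. I assume two-sided and carry both the t-test and the Wilcoxon-Mann-Whitney test.

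**Formula.** With n₁ responders and n₂ non-responders, t-test power is the probability that a noncentral t variable with n₁ + n₂ − 2 degrees of freedom and noncentrality δ = d·√[n₁n₂/(n₁ + n₂)] falls outside the two-sided 5% critical values. For the Wilcoxon test, both group sizes are first multiplied by the asymptotic relative efficiency for normal data, 3/π = 0.955.

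**Step 1: reproduce 134.**
- t-test, equal groups: 64 + 64 = 128 gives 0.801, so an even-split t-test does not give 134.
- Wilcoxon, equal groups: 66 + 66 gives 0.795 and 67 + 67 = 134 gives 0.801, an exact match.
- t-test at about 60:40: 80 + 54 = 134 gives 0.805, also consistent.
- One-sided versions give 102 (t-test) and 106 (Wilcoxon), so two-sided is the better reading.

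**Step 2: vary the split at N = 134.** Group sizes are 134 × response rate, rounded. For example, at 85%: n₁n₂/(n₁ + n₂) = 114 × 20/134 = 17.0, so δ = 0.5 × √17.0 = 2.06. At 67 + 67 the corresponding values are 33.5 and 2.89.

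| Response | Responders / non-responders | Power, t-test | Power, Wilcoxon | Detectable d at 80% power (t-test) |
|---|---|---|---|---|
| 56% | 75 / 59 | 0.81 | 0.80 | 0.49 |
| 60% | 80 / 54 | 0.80 | 0.79 | 0.50 |
| 70% | 94 / 40 | 0.75 | 0.73 | 0.53 |
| 85% | 114 / 20 | 0.53 | 0.52 | 0.68 |

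**Step 3: locate the crossing point.** On the t-test, 82/52 (61% response) gives 0.800 and 83/51 gives 0.797. Power is therefore at the stated level from 56% to about 61% response and below it for the rest of the cited range. On the Wilcoxon reading it is at 80%, to rounding, only at the 56% end.

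**Step 4: scale of the shortfall.** Holding 80% power for d = 0.5 would take 152 patients (t-test) or 159 (Wilcoxon) at 70% response, and 249 or 260 at 85%. This shows the size of the gap and is not a proposal to enlarge the study.

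**Step 5: losses, by assumption only.** The article gives no loss rate. If 10% were not evaluable (134 × 0.9 ≈ 121), t-test power would be 0.77 at 56%, 0.70 at 70% and 0.49 at 85%.

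**The case against.** Several points on the other side are sound.

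- **The arithmetic of 134 is not wrong.** It reproduces exactly in one variant and closely in another. The 60:40 t-test variant would mean that some imbalance was already allowed for, at a rate inside the cited range. The article cannot distinguish the two, so a 1:1 assumption cannot be attributed to the authors.
- **The 56–85% range is literature background.** It is not a planning rate stated for this study. A reader might infer that the plan expects up to 85% response and has ignored it; the text does not say so.
- **A reader might also infer that power is about 53% throughout.** It is not: that value belongs to the 85% end alone, and at 56% the stated 80% holds.
- **Not naming the test, the ratio or a dropout allowance is not a fault here.** A condensed article may leave these to the full protocol or analysis plan. Nor does the text support saying that all 134 must have a week-7 value: mixed models are planned, self-ratings are weekly, and clinician ratings are taken three times.
- **Other analyses do not depend on the split.** The study is exploratory, and its correlation and regression analyses of continuous psychometric change are not tied to responder status. The authors also undertake to report effect sizes beside p values, which limits misreading of null results.

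What remains is that the article prints one power figure for one named contrast and sets recruitment by it. That figure does not carry across most of the response rates the same article cites. An exploratory aim does not make it accurate, and the promised multiple-comparison correction can only lower the power of each test.

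**Conclusion.** The point stands in limited form. The sample size calculation is reproducible, but its 80% power is conditional on a split that the study does not control. Across the cited 56–85% response, power for one two-sided test of d = 0.5 falls from about 80% to about 53% (t-test) or 52% (Wilcoxon), passing through about 75% or 73% at 70% response. The shortfall begins above about 61% response on the t-test reading.

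The result assumes two-sided testing, one of the two tests that reproduce 134, all 134 patients classified, and no correction for multiplicity. It also assumes that this sample's response rate lies somewhere in the cited range, which the article does not state as a design assumption. The conclusion is that the power statement is incomplete and too favourable over most of that range. It is not that the sample size was miscalculated or that the study cannot meet its exploratory aims.

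**What to change.** Keep n = 134 and rewrite the last sentence of the Power calculation section so that power is conditional on the responder split. For example: with 134 evaluable patients and a two-sided t-test at 0.05, the comparison has 80% power to detect d = 0.49 at 56% response, 0.50 at 60%, 0.53 at 70% and 0.68 at 85%. Equivalently, power for d = 0.5 is 0.81, 0.80, 0.75 and 0.53. If the Wilcoxon test was the one used, give its power values instead (0.80, 0.79, 0.73 and 0.52). Say that the figures are for a single test before multiple-comparison correction.

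A further line for an assumed share of non-evaluable patients is optional and should be labelled as an assumption.

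The cost is a few sentences and a less favourable headline figure. No extra patients, visits or samples are needed.
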